### Outcomes and Measures

Clinical outcomes will be assessed using validated screening scales for self-reported symptoms, including Perceived Stress Scale (PSS-10; a score of ≥10 indicates a likely moderate or high stress) [55], the 7-item GAD scale (GAD-7; a score of ≥10 indicates likely generalized anxiety disorder) [56], the Patient Health Questionnaire-9 (PHQ-9; a score ≥10 indicates likely MDD) [57], and the Brief Resilience Scale (BRS; mean scores ranging from 1.00 to 2.99 indicate low resilience, from 3.00 to 4.30 suggest normal resilience, and from 4.31 to 5.00 suggest high resilience) [58,59].Validated scales have been chosen to better understand self-reported symptoms and potential symptom severity and to screen for the likely presence of psychopathology. These scales are not intended as diagnostic tools but instead are to identify risk factors and early symptoms of potential mental disorders such as depression and anxiety disorders. In addition, we will assess burnout using the Maslach Burnout Inventory (MBI) [60]. The MBI-Educators Survey will be used in this case, which is a version of the original MBI for use with educators, including teachers, administrators, other staff members, and volunteers working in any educational setting [61]. The primary outcome measures will be prevalence of moderate-to-high stress, burnout, likely GAD, likely MDD, and low resilience at baseline in subscribers of Wellness4Teachers. Other primary outcome measures will be changes in prevalence of moderate-to-high stress, burnout, likely GAD, likely MDD, and low resilience as well as changes in mean scores on the PSS-10, MBI, GAD-7, PHQ-9, and the BRS from baseline to 6 weeks, 3 months, and 6 months. Secondary outcome measures will include sociodemographic, clinical, and professional correlates of moderate-to-high stress, burnout, likely MDD, likely GAD, and low resilience among subscribers of Wellness4Teachers at baseline. An exploratory outcome will be a measurement of the adoption of the Wellness4Teachers program by teachers in Alberta and Nova Scotia. This will be assessed by measuring the proportion of the target population (teachers in Alberta and Nova Scotia) who subscribe to the daily supportive text messages.

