### Statistical Analysis

Quantitative data from the surveys will be analyzed using SPSS (version 25, IBM Corp) [65]. Descriptive statistics will be provided for demographic, clinical, and burnout-related variables based on the province of residence. Cross-tabular analyses using the chi-square test will explore the differences between elementary and high school teachers with respect to demographic, clinical, and professional variables. Descriptive characteristics will be presented as numbers and percentages, and a 2-tailed *P*≤.05 will be used to determine statistical significance for all analyses. We will use the chi-square test and logistic regression analysis to identify demographic, clinical, and work-related correlates of anxiety, depression, stress, low resilience, and burnout for elementary and high school teachers separately. Furthermore, we will assess the impact of the Wellness4Teachers program in reducing moderate-to-high stress, burnout, likely GAD, likely MDD, and improving resilience among Wellness4Teachers subscribers by assessing the mean changes in these parameters from baseline to 6 weeks, 3 months, and 6 months using the 2-tailed paired *t* test. To assess the effects of the intervention against a control group, we will choose a defined period of 3 months during the study period (eg, from the beginning of November 2022 to the end of January 2023) and compare the prevalence and mean scores on standardized scales for stress, burnout, anxiety, and depression at 6 weeks for subscribers who have received the daily supportive text messages for 6 weeks (intervention group) to the baseline prevalence and mean scores on the same scales for new subscribers during the period (control group). Surveys with more than 50% missing responses will be omitted from data analysis. For the included survey responses, there will be no imputation for missing data, and the analysis and results will be based on completed survey data.

We will analyze qualitative data (obtained by audio recording and transcribing responses from key informant interviews) using thematic analysis with NVivo (version 9; QSR International). The results will be reported as themes and subthemes supported by verbatim quotes.

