## Results

The Wellness4Teachers program is expected to be launched in September 2022 when the new academic year is scheduled to begin. Enrollment will last for approximately 1 year, and data collection will continue for another 6 months. Study results will be disseminated with stakeholders in the education sector in Alberta and Nova Scotia and globally through workshops, conference presentations, and peer-reviewed publications.

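### The only controlled comparison uses a 3-month window still to be chosen, lets the same teacher count in both groups, and leaves out resilience and the 3- and 6-month surveys

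*Protocol article*

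**What the plan says.** The Protocol article, Statistical Analysis, describes two ways of judging the program's effect. The first is a paired t test of mean change from baseline to each follow-up, covering resilience as well as the other four outcomes. It has no control.

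The second is the controlled comparison. Its period is introduced with "we will choose a defined period of 3 months during the study period (eg, from the beginning of November 2022"; the example closes with January 2023. The intervention group is measured "at 6 weeks for subscribers who have received the daily supportive text messages for 6 weeks (intervention group"), and is compared "to the baseline prevalence and mean scores on the same scales for new subscribers during the period (control group"). The outcomes and time point are limited to this: "compare the prevalence and mean scores on standardized scales for stress, burnout, anxiety, and depression at 6 weeks".

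Outcomes and Measures lists as primary the changes in prevalence of all five conditions, low resilience included, and also "changes in mean scores on the PSS-10, MBI, GAD-7, PHQ-9, and the BRS from baseline to 6 weeks, 3 months, and 6 months". The Hypothesis section includes low resilience in the expected reduction of at least 20%. On timing, the Results section says "Enrollment will last for approximately 1 year, and data collection will continue for another 6 months", with launch expected in September 2022.

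**The concern.** Three features of the controlled comparison need attention.

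- **Shared members.** The window is about 13 weeks and the exposure lag is 6 weeks. A teacher who joins early in the window gives a baseline record to the control group and, six weeks later, a 6-week record to the intervention group. The article states no exclusion, pairing or clustering, so the groups are neither separate nor fully matched.
- **Open dates.** The plan defers the choice of window and offers only an example. As written, nothing prevents the choice from being made once data have accrued.
- **Coverage.** Resilience and the 3- and 6-month changes are primary, yet they get no controlled comparison. Their evidence is pre-post change in a program launched at the start of a school year, where calendar effects and regression to the mean cannot be told apart from a program effect.

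This is the only controlled evidence in the article for the second main objective, whether the program reduces these problems and improves resilience.

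**Working it through.** The article gives no sample size or overlap figure for this comparison. Its one sample size, 1043 baseline surveys, concerns prevalence and reproduces: 1.96² × 0.25 / 0.03² = 1067.1, and 1067.1 / (1 + 1066.1/45,000) = 1042.4, rounded up to 1043.

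**Inputs from the article.** Example window 1 November 2022 to 31 January 2023; lag 6 weeks; enrolment about 1 year; survey completion at most 20%; analysis of completed surveys. **Assumptions.** Even enrolment, equal response rates in the two groups, and within-person correlation ρ of 0.4 to 0.7.

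**1. Overlap among eligible subscribers.**
- Window: 30 + 31 + 31 = 92 days. Lag: 42 days.
- Control: enrolled 1 November to 31 January.
- Intervention: 6-week date inside the window, so enrolled 20 September to 20 December.
- Both: enrolled 1 November to 20 December, 92 − 42 = 50 days. Share 50/92 = 54%.
- Sensitivity to enrolment: if it declines after launch with a 90-day half-life, the shared teachers are 63% of the control group and 46% of the intervention group. With a 30-day half-life, they are 78% and 29%.
- Sensitivity to late replies: if 6-week surveys are answered one or two weeks late, the share is 43/92 = 47% or 36/92 = 39%.

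**2. Overlap among respondents.** A teacher is analysed in both groups only if both surveys are completed. Overlap f = 0.543 × P(answers at 6 weeks | answered at baseline):
- responses independent at 20%: 0.543 × 0.20 = 11%
- half answer again: 0.543 × 0.50 = 27%
- all answer again: 54%

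**3. Effect on the standard error if the groups are treated as independent.** With n per group and f·n teachers shared, Var(difference) = (2σ²/n)(1 − ρf). The independent-groups standard error is therefore too large by the factor 1/√(1 − ρf):

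| f | ρ = 0.4 | ρ = 0.7 |
|---|---|---|
| 11% | 2% | 4% |
| 27% | 6% | 11% |
| 54% | 13% | 27% |

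**4. Share of the enrolment year used.** Each group: 92/365 = 25%. Both together: 20 September to 31 January = 134 days, 134/365 = 37%.

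**5. Coverage, by setting the sections side by side.** Primary change outcomes: five scales at three follow-ups. Paired t tests: five scales at three follow-ups. Controlled comparison: four outcomes at one follow-up. The BRS at any time, and every scale at 3 and 6 months, have no control.

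**The case against.** The strongest reply is that several alarming readings go further than the article allows. Most of that reply stands.

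- A reader might infer that half of the analysed teachers sit in both groups. The 54% refers to eligible subscribers under even enrolment. With completion of at most 20%, the overlap among completed surveys may be nearer 11%, and it reaches 54% only if every baseline responder answers again.
- A reader might infer that false positives are inflated. With positive within-person correlation the error runs the other way. It also presumes an independent-groups test. The article names no test for this comparison, and an analysis plan that is not shown might deal with the overlap.
- A reader might infer that three quarters of the enrolment year is thrown away. That holds for each group singly; together they draw on 37%. The paired t tests are not confined to the window.
- A reader might infer that resilience and the later surveys go unanalysed. They are in the paired t tests; what they lack is a control.
- A reader might infer that the window leaves the comparison plainly underpowered. With about 276 surveys per group (5515 × 0.25 × 0.20), power for a 20% relative reduction runs from 23% at a control prevalence of 20% to above 99% at 88%. No general statement about power follows.

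The reply does not remove the open dates, the absence of any rule on shared teachers, or the missing controlled comparison for resilience and later time points. These follow from the text without assumptions.

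**Conclusion.** The concern holds in a limited form. The window is undetermined, its two groups can share teachers, and the comparison covers only part of the primary outcome set.

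The overlap is up to about 54% of eligible subscribers in the example window, and about 11% to 54% of respondents. Both figures rest on even enrolment, and the second also on equal response rates. If the groups are analysed as independent, the standard error is overstated by 2% to 4% at the low end and 13% to 27% at the high end, for correlations that are assumed. The result is lost precision, with no excess of false positives from this source.

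The open choice of dates is a separate weakness, and its effect cannot be quantified from the article. The article does not show that the sponsor means to choose the window after seeing results; it only fails to rule this out.

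**What to change.** Replace the window with one model over the whole enrolment period, fitted to all surveys of all five scales including the BRS. Use time since enrolment (0, 6 weeks, 3 months, 6 months) as the exposure and calendar month as a covariate, with subscriber as a random effect or GEE cluster. This uses every enrolment month, handles repeated records from one teacher, and removes the choice of dates.

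State its limit: surveys answered after enrolment closes have no concurrent baseline. Under even enrolment over 12 months, that is about 6/12 = half of the 6-month surveys and 3/12 = a quarter of the 3-month surveys.

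If a window is kept, fix its dates before any data are seen. Either assign each teacher to one group by enrolment date or account for the within-person correlation, and add the BRS.

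The cost is a change of analysis wording, slightly more analysis work, and some precision lost to calendar adjustment. No new data are needed. The model assumes that later subscribers resemble earlier ones given the covariates, which the present comparison assumes too.

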## Methods

### Study Design

This study will use a mixed-methods quantitative and qualitative cross-sectional survey design. Quantitative data will be collected using web-based–administered questionnaires through the University of Alberta REDCap platform [46], a secure web application for building and managing web-based surveys and databases. Qualitative data will be collected through key informant interviews.

The web-based questionnaires will be designed to collect demographic, professional, and clinical variables including stress, burnout, anxiety, depression, and resilience. Follow-up surveys will also include subscriber experience and satisfaction questions. Teachers in Alberta and Nova Scotia will be invited to subscribe to the Wellness4Teachers program through an advertisement organized in collaboration with Alberta Teachers Association, the Alberta School Boards Association, the Nova Scotia School Boards Association, and the Nova Scotia Teachers Union. The web-based surveys will be distributed to subscribers upon enrollment, at 6 weeks, 3 months, and 6 months. Key informant interview questionnaire will be developed to assess and explore the factors that contribute to stress, burnout, anxiety, and depression among teachers, the impact of the Wellness4Teachers program on the levels of these mental health variables in subscribers, and subscriber satisfaction with the daily supportive text messaging program.

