## Discussion

### Expected Findings

Stress, burnout, anxiety, and depression can have a significant impact on the health, lifestyle, psychological safety, and well-being of teachers, leading to low levels of resilience and reduced professional fulfilment. The psychological impact is likely to be more significant for those with prior mental health conditions or those who have been exposed to previous traumas. Mental health support for groups such as teachers require innovative techniques that can provide support for more teachers. This protocol outlines the use of mobile health technology as a convenient, cost-effective, and accessible means for implementing a psychological intervention for teachers who may be experiencing stress, burnout, anxiety, and depression, and improve their overall resilience.

The outcomes of this study will be evaluated with standardized and empirically validated questionnaires. The findings will contribute to knowledge on eHealth approaches in the education sector and will provide key information about the prevalence rates of stress, burnout, anxiety, depression, and low resilience as well as their correlates in teachers. The findings will also provide evidence of effectiveness for the use of daily supportive text messaging programs to address stress, burnout, anxiety, depression, and low resilience among teachers. Information from this study will thus be critical and useful for informing school policy and decision makers regarding psychological interventions for teachers, especially during the ongoing COVID-19 pandemic or similar stressful situations. We hope that the outcome of this study will promote the integration of supportive text messaging into many organizations’ occupational health programs to provide readily available psychological support to individuals who need it, while at the same time improving their overall resilience and promoting professional fulfilment.

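### The only comparison with a control group conditions just the intervention group on staying and answering at 6 weeks and measures controls at sign-up, so selective response and regression to the mean can bias it.

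*Protocol article*

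**What the plan says.** Entry is by self-subscription (Wellness4Teachers Program). Study Design sets the survey times: "The web-based surveys will be distributed to subscribers upon enrollment, at 6 weeks, 3 months, and 6 months".

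Statistical Analysis introduces the controlled comparison with "To assess the effects of the intervention against a control group, we will choose a defined period of 3 months during the study period". The intervention group contributes its scores "at 6 weeks for subscribers who have received the daily supportive text messages for 6 weeks (intervention group"). These are compared "to the baseline prevalence and mean scores on the same scales for new subscribers during the period (control group"). On missing data, "there will be no imputation for missing data, and the analysis and results will be based on completed survey data".

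The one regression named in the section is for another purpose: "We will use the chi-square test and logistic regression analysis to identify demographic, clinical, and work-related correlates". For the group comparison the article names neither a test nor an adjustment. Separately, it plans paired t tests of mean change from baseline to 6 weeks, 3 months and 6 months.

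The Limitations section covers non-diagnostic scales, representativeness, low response as a threat to sample size, and duration of effect. It mentions neither selective retention or response nor regression to the mean. Expected Findings nevertheless says: "The findings will also provide evidence of effectiveness for the use of daily supportive text messaging programs".

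**The concern.** The two groups are selected by different rules. To supply a score, an intervention subscriber must still be enrolled at 6 weeks and must answer the survey sent then. A control must only answer the survey sent at enrolment, so the control group includes people who will later leave or stop answering. The shared 3-month window balances calendar time. It does not balance retention, later response or time since sign-up.

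Two biases follow. If distressed teachers are less likely to stay or answer, the 6-week group is healthier by selection. If people subscribe when symptoms are unusually high, controls are measured near a peak, while the intervention group has had 6 weeks to drift back. Either could be read as an effect of the messages. This is the only analysis with a control group behind a main objective, and the article looks ahead to promoting the programme if findings are positive.

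**Working it through.** **The plan's own figure.** The article gives no sample size or power for this comparison. Its only sample size is for baseline prevalence: 95% CI, 3% margin, population 45,000. That reproduces: 1.96² × 0.25 / 0.03² = 1067.07 (using the unrounded normal quantile), and 1067.07 / (1 + 1066.07/45,000) = 1042.4, rounded up to 1043.

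**Inputs from the article.**
- Moderate-to-high depression symptoms among new subscribers of the earlier Text4Hope programme: 52.1%; moderate-to-high stress: 88.0% (Wellness4Teachers Program).
- Expected programme dropout: under 15% (same section).
- Survey completion: at most 20% (Sample Size Estimation).
- Hypothesised reduction: at least 20% (Hypothesis).

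**Inputs assumed here.** No treatment effect throughout; the completion ratio r; the correlation and sign-up strength in step 3; the group sizes in step 4.

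**Step 1: selective retention or response.** Let p be sign-up prevalence and r the 6-week completion rate of sign-up cases divided by that of non-cases. With unchanged symptoms, observed prevalence is q = p·r / (p·r + 1 − p), and the apparent relative reduction is 1 − q/p.

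| p | r | q | apparent reduction |
|---|---|---|---|
| 52.1% | 0.9 | 49.5% | 5% |
| 52.1% | 0.8 | 46.5% | 11% |
| 52.1% | 0.7 | 43.2% | 17% |
| 52.1% | 0.6 | 39.5% | 24% |
| 88.0% | 0.8 | 85.4% | 3% |

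For example, 0.521 × 0.8 = 0.4168, and 0.4168 / (0.4168 + 0.479) = 0.465.

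The ratio that alone yields a 20% reduction solves q = 0.8p. At 52.1%, q = 0.4168 and r = (0.4168/0.5832) / (0.521/0.479) = 0.66. At 88%, q = 0.704 and r = (0.704/0.296) / (0.88/0.12) = 0.32.

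**Step 2: dropout alone, as a bound.** If everyone still enrolled answered, and all of a 15% dropout were cases, then q = (0.521 − 0.15)/0.85 = 43.6%, a 16% reduction. This is an extreme, not an expectation.

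**Step 3: regression to the mean alone.** Simulated scores at sign-up and at 6 weeks were bivariate normal with correlation 0.6 to 0.9. The chance of signing up rose with the current score, so that subscribers averaged 0.22 to 0.74 SD above the teacher population. The case threshold was set to give 52.1% at sign-up. The apparent reduction ran from 1.5% (correlation 0.9, weakest selection) to 24% (correlation 0.6, strongest selection). Adding r = 0.8 gave 9% to 28%.

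**Step 4: chance of a significant result.** Comparing 52.1% with 46.5% at a two-sided 0.05, the probability of significance is about 0.42 with 500 per group and 0.70 with 1000 per group.

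**Step 5: people in both groups.** The example window, November to January, has 92 days. Someone who joins in the first 92 − 42 = 50 days reaches week 6 inside it. Under even enrolment, 50/92 = 54% of controls who later complete the 6-week survey would also supply an intervention score.

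**The case against.** Several points on the other side stand.

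- A reader might infer that the comparison is fixed as unadjusted. The article names no adjustment but rules none out, and covariate lists are commonly left to a fuller plan. The point therefore rests on the stated group definitions. Demographic adjustment would not by itself undo those.
- A reader might take the control group to be every new sign-up. Scores exist only for those who answered the baseline survey, expected to be at most 20%, so both groups are selected responders. The asymmetry is the further requirement on the intervention group to stay and answer at 6 weeks. Nor does the article say that an intervention subscriber must have completed a baseline survey.
- A reader might conclude that the bias must look like benefit. Nothing in the article shows that distressed teachers leave or fall silent more often, or that they subscribe at a peak. Opposite selection would hide a benefit.
- Effectiveness does not rest on this comparison alone. Changes from baseline are listed as primary outcomes, and the paired t test sets each completer against their own baseline. That removes between-person selection. It has no control group and leaves regression to the mean in place.
- Expected dropout under 15% makes the enrolment filter modest, so most of the larger effects in step 1 would have to come from survey non-response.
- Simply restricting controls to later completers would increase the overlap of people between groups. The remedy must deal with this.

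The article is open that this is a self-subscription programme, and a similar comparison was used for the earlier programme. That explains the design but does not make the groups comparable.

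**Conclusion.** The concern holds for the group definitions. The controlled comparison conditions one group on 6-week retention and response, measures the other when support was sought, and does not disclose either source of bias. With no true effect and 52.1% sign-up prevalence, a completion ratio of 0.8 gives an apparent 11% reduction, and about 0.66 reproduces the hypothesised 20%. At 88% prevalence a ratio of 0.8 gives about 3%, so the size depends strongly on the outcome. Regression to the mean could add to this.

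The completion ratios, correlations, selection strengths and group sizes are assumptions. Direction towards benefit is plausible but not established. The documents do not support saying that the comparison will show a false benefit, only that it cannot separate benefit from selection and regression to the mean.

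**What to change.** 1. As the main version of the comparison or as a sensitivity version, restrict controls to new subscribers in the window who later complete their own 6-week survey. Data collection continues for 6 months after enrolment, so this is feasible. Either let each person count in one group only, by a rule set in advance, or use a model that accounts for the same person appearing in both.
2. Adjust this comparison for the demographic and professional covariates already being collected, and say so in the plan.
3. Report the intervention group's own baseline scores, where available, beside the controls' baseline scores. Also report baseline scores of 6-week completers against non-completers. These tables show which way selection ran.
4. Report the result as an association. State in the limitations that selective response and regression to the mean after sign-up are not fully removed.

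All of this uses data already planned. The cost is a smaller control group, which may be marked given survey completion of at most 20%, and a less emphatic claim. If overlapping people were kept in the intervention group only, then under even enrolment about 46% (42/92) of the restricted controls in the example window would remain. A model allowing for repeated people avoids that loss.
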